## Abstract

**Background:**

Unemployment affects millions of people worldwide and, beyond its economic impact, has severe implications for people’s well-being and mental health. Different programs have been developed in response to this phenomenon, but to date, job-search interventions have proved to be most effective, especially the JOBS II program. The JOBS II program proved not only to be effective for re-employment but also has a positive impact on beneficiaries’ mental health (ie, reduces anxiety or depression). However, by now, this evidence-based program has been delivered only on site in the various countries where it was implemented. In the digital era, web-based alternatives to such programs are highly needed because they have the advantages of scalability and cost-effectiveness.

**Objective:**

In this context, we aim to investigate the efficacy of iJobs, the web-based adaptation of the JOBS II program, on job-search intensity and effort, the quality of job-search behaviors, and job-search self-efficacy. Further, 1 month after the intervention, we will also assess the employment status and the satisfaction with the job (if applicable). This study will also investigate the effect of iJobs on well-being and mental health (ie, anxiety and depression).

**Methods:**

This study is a 2-arm randomized controlled trial. The 2 independent groups (intervention vs waiting list control group) will be crossed with 3 measurement times (ie, baseline, the postintervention time point, and 1-month follow-up). The design will be a 2 (intervention vs control) × 3 (baseline, the postintervention time point, and 1-month follow-up) factorial design. iJobs is a 2-week intervention consisting of 6 modules: an introductive module and 5 modules adapted from the original JOBS II program to the web-based setting and Romanian population. The web-based intervention also has a human component, as beneficiaries receive personalized written feedback after each module on the platform from a team of psychologists involved in the project.

**Results:**

The enrollment of study participants started in June 2023 and is expected to end in May 2024. The data collection is expected to be completed by July 2024. The results are expected to be submitted for publication in the summer of 2024.

**Conclusions:**

This study is the first large-scale randomized controlled trial aiming to test the efficacy of a web-based adaptation of the JOBS II program. If our results support the efficacy of iJobs, they will offer the premise for it to become an evidence-based, accessible alternative for unemployed people in Romania and might be implemented in other countries.

**Trial Registration:**

ClinicalTrials.gov NCT05962554; https://clinicaltrials.gov/study/NCT05962554

**International Registered Report Identifier (IRRID):**

PRR1-10.2196/55374

## Introduction

### Background

Losing a job or not being able to find a job after finishing studies is a stressful life event—unemployed people struggle not only with financial strain but also with the stigma around it. Unemployment has become a vicious spiral that negatively affects individuals’ lives. As time passes, the motivation of unemployed people declines, which affects the intensity of the job-search process [1]. Hence, the chances of gaining re-employment decrease, and the well-being of unemployed people worsens. This can finally lead to mental health impairment (eg, depression and anxiety), and an essential moderator in this relationship is the duration of unemployment [2]. The alarming aspect of this phenomenon is not only how bad the impact of unemployment is at the individual level but also how many people are experiencing it worldwide.

In 2022, the unemployment rate was 6.1% in the European Union, but it is spread differently between countries, and more importantly, it is distributed asymmetrically within the same country regions. In Romania, the lowest percentage of unemployment is registered in the North-West and West regions (3.1% and 3.7%), whereas the highest rates range from 6.6% to 8.8% in the North-East and South regions [3]. From an economic perspective, the youth unemployment rate (people aged between 15 and 29 years) is more concerning. Romania’s Central and South regions register youth unemployment rates above 14.7%, and the European Union rate is 11.3% [3].

Various national programs and strategies are being developed to fight this phenomenon. However, the need for alternative solutions that promote employment (shortly after job loss) and well-being among unemployed people is evident. Efficient alternatives to classic governmental programs are job-search interventions. The JOBS II intervention [4] is one of them. JOBS is a job-search intervention intended to promote re-employment and mental health that differentiates itself from others by being studied in and adopted by many countries over the years, such as Finland [5], China [6], Ireland [7], Netherlands, Sweden, and South Korea [8], South Africa [9], or Germany [10].

Existing theories emphasize that unemployment is a cause of distress because unemployed people lose an essential social role (ie, status) and lack psychological basic needs fulfilled by one’s job (eg, time structure, social contact, activity, and financial security) [2]. Unsuccessful attempts to gain re-employment reduce the motivation of job seekers and affect their sense of competency and positive self-evaluations. In time, this can lead to mental health issues (ie, anxiety and depression). According to the results of a recent systematic review [11], JOBS improved participants’ self-esteem, self-efficacy (ie, job-search self-efficacy; JSSE), and ability to deal with setbacks (ie, inoculation against setbacks), which improved their well-being and mental health (on both the short and long term). Additionally, these coping mechanisms and job-search skills promoted and enhanced by JOBS are crucial for obtaining re-employment in a shorter period and obtaining a more qualitative job. Employment success and quality are predicted by job-search intensity and effort and job-search quality [12]. JOBS promotes job-search behaviors (JSBs; eg, beneficiaries make their job-search schedule) and the quality of those behaviors (eg, networking and practicing interviews).

The program’s effectiveness and popularity are based on its structure. It is a short-term intervention of 5 group sessions, encompassing almost all the components proven effective for job-search interventions [13]: *active learning, job-search skills, inoculation against setbacks, social support,* and *referent power.* During JOBS, participants learn the tasks they have to perform from the role of a job seeker and improve the necessary skills through group discussions, case studies, and role-playing exercises. They discover how to overcome potential setbacks in the re-employment process by brainstorming coping strategies, practicing their problem-solving skills, and receiving continuous social support from the trainers and beneficiaries.

However, JOBS is an on-site intervention that requires many resources to be delivered. This format restricts the number of beneficiaries and implies costs for both the organizers (eg, trainers and materials) and unemployed people to participate (eg, transportation fees). In the digitalization era and in the recent context of the COVID-19 pandemic that drastically changed the way we work and learn, it would be worthwhile to explore the efficacy of this intervention in a web-based format. An internet-delivered intervention can be an immediate solution at hand for those who just lost their jobs and could address more people at a time. Some possible advantages of such an alternative may also be the reduced costs and increased flexibility (ie, it is asynchronous).

iJobs is the first web-based adaptation of the JOBS II intervention, which was previously studied in a feasibility and acceptability trial [14]. The results were promising in terms of satisfaction with iJobs, so a further study testing its’ efficacy is worthwhile because it can provide information regarding the program’s impact on relevant outcomes.

### Specific Objectives

This study aims to investigate the efficacy of iJobs on job-search intensity and effort, the quality of JSBs, and JSSE. We will also assess the employment status and satisfaction with the job (for those who will be employed) 1 month after the intervention. This study will also investigate the effect of iJobs on well-being and mental health.

As a secondary objective, we will evaluate the moderating effects on re-employment of factors such as age, educational level, unemployment period, financial strain, and the mediating effects of job-search intensity, job-search quality, and self-efficacy on re-employment.

Since this is the first large-scale study on a web-based adaptation of the JOBS II program, as stated in the feasibility study [14], we will also evaluate the satisfaction with the intervention, the system usability, and the treatment adherence for the intervention groups.

Specifically, we will test the following hypotheses:

H1: iJobs will increase the job-search intensity (H1a) and job-search effort (H1b) in the intervention group compared to the control group.H2: iJobs will increase the quality of job-search behaviors in the intervention group compared to the control group.H3: iJobs will increase job-search self-efficacy in the intervention group compared to the control group.H4: iJobs will increase self-esteem (H4a), inoculation against setbacks (H4b), and psychological capital (H4c) in the intervention group compared to the control group.H5: iJobs will decrease future career anxiety (FCA; H5a), depression (H5b), anxiety (H5c), and mental health complaints (H5d) in the intervention group compared to the control group.H6: The job-search intensity (H6a), job-search quality (H6b), and JSSE (H6c) will mediate the effect of iJobs on re-employment.H7: Age (H7a), educational level (H7b), unemployment period (H7c), and financial strain (H7d) will moderate the effect of iJobs on re-employment. iJobs will have stronger effects on re-employment for younger participants, participants with higher educational levels, participants with a shorter period of unemployment, and participants with lower levels of financial strain.

## Methods

### Ethical Considerations

Ethical approval regarding human subject research was obtained from the West University of Timișoara’s Scientific Council in May 2023 based on an application containing this study’s aim, procedure, measures, and materials (32005/17.05.2023). This study was registered as a clinical trial on ClinicalTrials.gov (NCT05962554). Participants will give their informed consent and, as per the European Union’s regulations, accept the General Data Protection Regulation statement when enrolling in the program: all the data from the questionnaires completed during and after the intervention is anonymous, their identity on the iJobs platform is protected by a random identification code that serves as the username, and they can withdraw from this study at any point. Participants who complete the follow-up measurements will be included in a raffle and can win either a backpack or an insulated bottle.

### Trial Design

This study is a 2-arm randomized controlled trial (RCT) that will test the efficacy of a web-based adaptation of iJobs. Participants will be randomly assigned (1:1 allocation) to either the intervention group, which benefits from the iJobs program, or a waiting list control group that will also receive the iJobs intervention 2 weeks after the intervention group finishes it. The 2 independent groups (intervention vs waiting list control group) will be crossed with 3 measurement times (ie, baseline, the postintervention time point, and 1-month follow-up). Hence, the design will be a 2 (intervention vs control) × 3 (baseline, the postintervention time point, and 1-month follow-up) factorial design.

### Participants and Recruitment

Eligible participants are unemployed Romanian adults. We will include in this study participants who (1) are unemployed and looking for a job, (2) work as volunteers and are looking for a paid job, (3) are aged between 18 and 60 years, and (4) have a PC or a laptop and basic digital skills. We will exclude the participants who do not have internet access or are lacking in availability during the 2-week program period.

Our recruitment strategy is to post an overview of iJobs on social media (ie, Facebook and LinkedIn), using paid advertising targeting job seekers, and on web-based newspapers. We will also promote iJobs on Employment Force Agencies and Recruitment Agencies across Romania.

### Intervention

iJobs is a web-based adaptation of the JOBS II program: *a manual for teaching people successful job-search strategies* [4]. iJobs is a 2-week intervention with 6 modules: an introductive module and 5 modules adapted from the original JOBS II program. iJobs will be delivered via TalentLMS (Epignosis), a web-based, cloud-based learning management system. iJobs’ visual interface is depicted in Figure 1. The intervention was previously tested in a feasibility and acceptability open-label trial using a different platform [14]. A brief description of iJobs modules can be found in Textbox 1. The program’s content is audio and text based, but the participants will answer in writing to all of the exercises.

iJobs is an asynchronous program, so the component of mutual social support between beneficiaries is absent. Compared to the JOBS II program, the participants interact via messages only with the counselors involved in the feedback process. The counselors were previously instructed about iJobs’ aim, content, and feedback process.

**Figure 1 figure1:**
[figure not shown]
iJobs’ interface samples. From authentication to the main app dashboard, a preview of video material, and completing of an exercise on the platform.

Overview of iJobs modules. Brief description of each module’s content.
**Introductive module**
Participants will watch a short video explaining the platform’s main features (eg, how to complete exercises during the program and send messages to the counselors). At the end of the module, the participants must complete a questionnaire (eg, the pretest measures for the intervention group) to be enrolled in the intervention.
**Discovering your job skills**
Participants will identify their strengths and learn how to demonstrate them during interviews from audio case studies that illustrate effective versus ineffective interviews.
**Dealing with obstacles to employment**
Participants will identify possible obstacles and challenges in the employment process and explore how they can address them during interviews.
**Finding job openings**
Participants will learn about networking and how their extended network can help identify job opportunities (eg, they complete an informational interview exercise).
**Resumes, contacts, and interviewing**
The fourth module focuses on resumes (participants will analyze a resume and then create their curriculum vitae) and includes interview exercises from both the role of the candidate and the employer.
**Complete interview and planning for setbacks**
Participants will integrate the information learned during the program into a complete interview. Ultimately, they will anticipate obstacles and prepare strategies for overcoming them in the re-employment process.

### Procedure

The study procedure is presented in Figure 2. In the enrollment phase, an overview of the program and a link to open the iJobs presentation website [15] will be posted on social media (ie, paid advertising on Facebook and LinkedIn, web-based newspapers, and employment agency sites). Those who want to participate will have to complete a registration form, give their informed consent, and accept the General Data Protection Regulation statement. Eligible participants will be randomly allocated to either the intervention or the waiting list control group (1:1 allocation).

**Figure 2 figure2:**
[figure not shown]
Study design and procedure overview. t0: 2-3 weeks before iJobs; t1: randomization within 1 week before iJobs and pretest assessments for both groups; t2: posttest assessments within 1 week after iJobs for both groups; the control group starts now iJobs; t3: follow-up screening 1 month after iJobs for the intervention group; posttest assessments for the control group at the end of iJobs; t4: follow-up screening 1 month after iJobs for the waiting list group.

The participants from the intervention group will receive an email with the iJobs calendar and brief instructions. Afterward, they will receive an email with the platform login information. The username will be a random combination of digits (eg, IJ105) to ensure participants’ anonymity during the program. The account password is generated automatically by the platform. Once participants access their accounts, an introductive module containing the baseline measures questionnaire will be available on the platform. Meanwhile, the waiting list control group participants will receive an email with the iJobs period and a link to the baseline questionnaire.

On the iJobs’ platform, each module will be available for completion for 27 hours. After participants receive personalized written feedback on the platform from the team of counselors involved in the program, the following module will become automatically available for completion. After the last module, the posttest questionnaires will be available on the platform for 48 hours.

Further, 2 weeks after the intervention group finishes iJobs, the control group will start the intervention and go through the abovementioned steps. The questionnaire from the introductive module is the posttest measure for the control group.

Additionally, 1 month after the intervention, the participants who complete the posttest measures will be contacted to complete a brief questionnaire that evaluates their employment status and JSBs.

An overview of this study’s period is presented in Table 1.

**Table 1 table1:** Study timeline. Time points and outcome assessments for the intervention group and waiting list group from enrollment to follow-up.

			Time point^a^								
			Enrollment (t0)		Randomization and pretest measurement (t1)		Posttest measurement (t2)		Follow-up intervention group (t3)		Follow-up control group (t4)
Enrollment			✓								
Eligibility screen			✓								
Informed consent			✓								
Randomization					✓						
Intervention group					✓		✓				
iJobs (intervention group)					✓						
Waiting list control group					✓		✓				
iJobs (control group)							✓				

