**Assessments^b^**											
	Job-search intensity and effort			✓		✓		✓		✓	
	Job-search quality			✓		✓		✓		✓	
	Job-search self-efficacy			✓		✓		✓		✓	
	Self-esteem			✓		✓					
	Inoculation against setbacks			✓		✓					
	Psychological capital			✓		✓					
	Future career anxiety			✓		✓					
	Depression			✓		✓					
	Anxiety			✓		✓					
	Mental health complaints			✓		✓					
	Physical health	✓									
	Financial strain	✓									
	Sociodemographics	✓									
	Treatment adherence					✓		✓			
	Treatment satisfaction					✓		✓			
	System usability					✓		✓			
	Employment status	✓						✓		✓	
	Job quality (if applicable)							✓		✓	

^a^t0: 2-3 weeks before iJobs; t1: randomization within 1 week before iJobs and pretest assessments for both groups; t2: posttest assessments within 1 week after iJobs for both groups; the control group starts iJobs; t3: follow-up screening 1 month after iJobs for the intervention group; posttest assessments for the control group at the end of iJobs; t4: follow-up screening 1 month after iJobs for the waiting list group.

^b^For a detailed description, see the *Outcomes* section.

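### The t2 posttest has unreconciled timing that differs by arm: the Procedure implies about 0-2 days after the course for intervention and about 2 weeks for controls, Table 1 says within 1 week for both

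*Protocol article*

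**What the plan says.** The timing of t2 is described in several places in the protocol article.

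- **Procedure, intervention arm:** "After the last module, the posttest questionnaires will be available on the platform for 48 hours".
- **Procedure, control arm:** "The questionnaire from the introductive module is the posttest measure for the control group". On when that course begins: "2 weeks after the intervention group finishes iJobs, the control group will start the intervention and go through the abovementioned steps". Trial Design also gives 2 weeks.
- **Procedure, module access:** "each module will be available for completion for 27 hours". The Intervention section counts the introductive module among the six: "iJobs is a 2-week intervention with 6 modules: an introductive module and 5 modules adapted from the original JOBS II program".
- **Table 1, footnote a** (the Figure 2 legend has almost the same wording): "t2: posttest assessments within 1 week after iJobs for both groups; the control group starts iJobs".

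The pretest also uses different routes. Table 1 sets it within the week before iJobs for both groups. The Procedure puts the intervention pretest inside the introductive module on the platform and sends controls a link by email.

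Three other statements matter here. Data Analysis makes the baseline-to-postintervention comparison the main contrast for all primary and secondary outcomes, uses those who completed the pretest, and fits a linear mixed model without imputation. The Procedure contacts only posttest completers at 1 month. Results reports pretest-to-posttest loss of 11/25 in the intervention arm and 10/38 in the control arm.

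**The concern.** In a randomised comparison of change, the outcome should be taken at the same time since randomisation in both arms. If it is not, the group-by-time term mixes the effect of the course with the effect of extra elapsed time in one arm. During that time people may find work, lose motivation or change mood whatever their allocation.

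Recall periods make this sharper. Job-search intensity and effort, anxiety and depression all ask about the past 2 weeks, and so does the sample item for mental health complaints. A shift of about 2 weeks between the arms means that they report on almost entirely different periods.

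A second, smaller matter is access. Someone who finishes the course and wants to answer on day 3 to 7 is on time under Table 1, but finds the questionnaire closed under the Procedure. That person would lose the posttest and, because of the contact rule, the 1-month assessment as well.

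**Working it through.** **1. Reported loss reproduced.** 11/25 = 44.0% and 10/38 = 26.3%. Completers are 25 − 11 = 14 and 38 − 10 = 28, total 42. All agree with Results.

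**2. Window lengths.** One week is 7 × 24 = 168 hours.

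| Source | Arm | Access to t2 | Share of 168 h |
|---|---|---|---|
| Table 1, Figure 2 legend | both | 168 h | 100% |
| Procedure | intervention | 48 h | 48/168 = 29% |
| Procedure, if the module limit applies (inference) | control | 27 h | 27/168 = 16% |

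Both shorter windows can fit inside a week, so the lengths alone are not a strict contradiction. They do admit different responders.

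**3. Position of the windows.** Let day 0 be the day on which the intervention group finishes.

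- Intervention t2: day 0 to 2 (48 hours).
- Control t2: about day 14, when the control course and its introductive module open.
- Table 1 limit for both: day 7.

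Control t2 at day 14 is 14 − 7 = 7 days past the Table 1 limit. This is the firm conflict, and it does not depend on the 27-hour inference.

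**4. Gap between arms.** 14 − 2 = 12 to 14 − 0 = 14 days. Counted from the start of the 2-week course, the intervention arm is measured at 14 + 0 to 14 + 2 = 14 to 16 days and controls at 14 + 14 = 28 days.

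**5. Overlap of 2-week recall.** Overlap = 14 − gap, so 14 − 14 = 0 to 14 − 12 = 2 days. The intervention arm reports mainly on the course fortnight, and controls mainly on the fortnight after it. With both arms assessed inside the same 7 days, the gap between any two respondents is at most 7 days and the overlap at least 14 − 7 = 7 days.

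**6. Sensitivity.** If the control introductive module opened up to a week before the control course, mirroring t1, control t2 would fall on day 14 − 7 = 7 to day 14. The gap would be 7 − 2 = 5 to 14 days, and only the earliest answers would meet the Table 1 limit.

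**7. Does the reported loss point to the windows?** The difference is 44.0 − 26.3 = 17.7 percentage points (95% CI about −6 to 42; Fisher p = 0.18). The larger loss is in the arm with the longer of the two Procedure windows. The counts therefore do not show that short windows cause loss.

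**The case against.** The strongest defence is that Table 1 is a schedule and the Procedure describes platform access. A questionnaire open for 48 hours lies inside the scheduled week, so nothing conflicts for the intervention arm. That stands: for this arm the difference is unreconciled, not contradictory. It does not help the control arm, whose posttest is tied to a module that opens after the week has passed.

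A reader might infer more than the text supports, in three ways.

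- **That the control posttest closes after 27 hours.** No sentence says so. It follows only if the general module limit covers the introductive questionnaire, which might instead be an entry step without that limit.
- **That late answers are discarded.** The article gives no rule for a questionnaire returned late or for reopening access, and such detail is commonly left to the full protocol.
- **That the 44% versus 26% loss reflects the windows, or that a power loss can be computed from it.** The intervention posttest opens only after the last module, so people who stopped early never reached it. The article does not say how many of the 11 finished the course, and it could be none. Controls must also complete their questionnaire to enter the course, an incentive that the intervention arm lacks. Nor can these losses be applied to all 180 planned participants: the dropout denominators total 25 + 38 = 63 of 130 randomised.

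A last objection is that a longer control window could let controls answer after starting the content. It is a fair condition on the remedy. With the control course starting at 2 weeks, a window ending on day 7 closes before any control content; the remedy should state this as a rule in any case.

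**Conclusion.** The point holds as one about timing. The Procedure and Trial Design on one side, and the Figure 2 legend and Table 1 footnote on the other, cannot all be followed for the control arm. Followed literally, the Procedure separates the arms' endpoint assessments by 12 to 14 days, with 0 to 2 days of shared recall on the 2-week scales. If the control introductive module opens a week early, the separation may be as small as 5 days. The direction of any resulting bias cannot be stated from the documents.

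The 48-hour closure is a secondary risk to completeness. It affects only people who finish the course and would answer on days 3 to 7; their number is unknown and may be close to zero. No standard-error or power figure is justified, and the differential loss reported so far should not be cited as support.

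The point merits correction because every primary and secondary outcome depends on t2 and the remedy is inexpensive.

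**What to change.** Reconcile Trial Design, Procedure, the Figure 2 legend and Table 1 so that they state one t2 rule:

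1. Use a single calendar-matched window in both arms: the 7 days after the intervention group finishes iJobs.
2. Send the control posttest by a separate link instead of placing it in the introductive module. In every case, close it before controls can open any content module.
3. Use the same opening and closing rule for the t1 questionnaire in both arms, closing before the first content module.

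This fixes the assessment window only. When the control course starts is for the sponsor to settle and state consistently.

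The cost is a platform setting, one additional link and short text corrections. Intervention outcome dates would spread over up to 7 days instead of 2, which Table 1 already allows. Controls would answer before entering their course, not as part of entering it, so they may need a reminder. Sessions already run keep their original timing.

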## Results

The enrollment of study participants started in June 2023 and is expected to end in May 2024. Until September 2023, we organized 2 iJobs sessions. Out of the 130 randomized participants, we collected complete data (ie, pre- and postintervention) from 42 participants (*n*_intervention group_=14, *n*_control group_=28). The dropout rate from pretest to posttest in the intervention group was 44% (11/25) and 26% (10/38) in the waiting list control group (see Figure 3 for a flowchart). The data collection is expected to be completed by July 2024. The results are expected to be submitted for publication in the summer of 2024.

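### The control posttest is the entry questionnaire for the deferred iJobs and no route is stated for controls who do not start, so control outcomes are observed conditional on uptake

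*Protocol article*

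**What the plan says.** The protocol article states a route for each baseline and posttest questionnaire, mostly in Methods, Procedure (the text after Figure 2).

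- **Control baseline:** "the waiting list control group participants will receive an email with the iJobs period and a link to the baseline questionnaire". This lies outside the programme.
- **Control posttest:** "The questionnaire from the introductive module is the posttest measure for the control group". Controls reach that module when their own programme opens: "2 weeks after the intervention group finishes iJobs, the control group will start the intervention and go through the abovementioned steps".
- **What that questionnaire does:** Textbox 1 (Introductive module) says "the participants must complete a questionnaire (eg, the pretest measures for the intervention group) to be enrolled in the intervention".
- **Intervention posttest:** "After the last module, the posttest questionnaires will be available on the platform for 48 hours".
- **One-month follow-up:** "the participants who complete the posttest measures will be contacted to complete a brief questionnaire that evaluates their employment status and JSBs".

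The Employment Status paragraph places the employment question at follow-up, and Table 1 shows it at t0, t3 and t4 but not at t2. On incentives, Ethical Considerations says: "Participants who complete the follow-up measurements will be included in a raffle".

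Under Data Analysis, everyone eligible with a pretest is kept in a linear mixed model without imputation. The baseline-to-post contrast serves all primary and secondary outcomes.

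**The concern.** The control arm supplies the untreated comparison. Its posttest should be obtained whether or not a person still wants the programme. The stated procedure instead ties that posttest to programme entry. A control who has found work, feels better or has lost interest has less reason to begin a two-week job-search course, and the text gives no other way of obtaining that person's outcome.

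These states bear directly on search intensity, self-efficacy, career anxiety, depression and anxiety. They arise after baseline. They are not recorded at t2, and because follow-up goes only to posttest completers, they are not picked up later either. At stake is whether the control mean in the main contrast represents all pretested controls or mainly those still interested in iJobs.

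**Working it through.** **1. Is the rule in the text?** Put the two statements side by side. Procedure identifies the control posttest with the introductive-module questionnaire. Textbox 1 makes that questionnaire the step that enrols a person in iJobs. Together they mean that giving a posttest and entering the deferred programme are one act. The article had a programme-independent route for the same people at baseline (the emailed link) and does not repeat it at posttest.

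**2. Reproduce the reported losses (Results).** The text says: "The dropout rate from pretest to posttest in the intervention group was 44% (11/25) and 26% (10/38) in the waiting list control group".

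| Arm | Pretested | No posttest | Proportion | Measured |
|---|---|---|---|---|
| Control | 38 | 10 | 10/38 = 0.263 | 28/38 = 73.7% |
| Intervention | 25 | 11 | 11/25 = 0.440 | 14/25 = 56.0% |

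The measured counts (28 + 14 = 42) match the 42 complete cases reported. Fisher's exact test for the difference in loss gives p = 0.18. No reason is given for any loss.

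**3. How far could selection move the means?** Let D be the mean difference, in SD, between unmeasured and measured participants, on an outcome scored so that higher is better. D is an assumption, because the documents give no outcome data. Within one arm:

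shift of completer mean = −(proportion missing) × D

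Controls alone:

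| D | 0.263 × D |
|---|---|
| 0.2 | 0.05 SD |
| 0.5 | 0.13 SD |
| 0.8 | 0.21 SD |
| 1.0 | 0.26 SD |

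**4. Add the other arm.** For intervention minus control:

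net bias = 0.263 × D(control) − 0.44 × D(intervention)

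- D = 0.5 in controls only: +0.13 SD, in favour of iJobs.
- D = 0.5 in both arms: (0.263 − 0.44) × 0.5 = −0.09 SD, against iJobs.
- D = −0.5 in controls only (those lost are doing worse): −0.13 SD, against iJobs.
- The net bias is zero when D(intervention) = (0.263/0.44) × D(control) = 0.60 × D(control).

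The sign therefore depends on two unknown gaps.

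**5. Scale.** The protocol's 132 participants give 66 per arm. For a simple posttest comparison at two-sided 5% and 80% power (the significance level is my assumption; the article states none), the detectable difference is (1.960 + 0.842) × √(2/66) = 0.49 SD. A shift of 0.13 SD would be 0.13/0.49 = 27% of that.

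**6. Does the mixed model deal with it?** It keeps an unmeasured control through the baseline value, so any part of D predictable from baseline is reduced. The shifts above are for raw completer means, not for the planned estimator. The part of D due to events after baseline remains, and nothing collected at t2 identifies it.

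**The case against.** A reader might infer that the controls doing best drop out, so that the comparison is biased towards iJobs by 0.13 to 0.26 SD. The documents do not support that, for these reasons:

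- No reason is reported for any of the 10 missing controls. Nothing bars an employed control from answering, and the form comes before the five content modules, so no module work is needed.
- 74% of pretested controls did answer, so the selection is partial.
- The direction is open. The Background section says motivation falls as unemployment lasts and ties this to poorer well-being, so disengaged controls could be doing worse. Controls who found work might also score lower on search intensity and higher on self-efficacy, which pulls outcomes in opposite directions.
- The intervention arm loses more (44%), through its own gate after the last module.
- The mixed model uses baseline data, and sensitivity analyses for missing data may sit in an analysis plan that is not shown.

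All of this stands against a directional claim or a fixed size.

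Two further objections have partial force. First, a condensed article may omit reminders or other contact with non-starters, and the Figure 2 legend and Table 1 footnote do schedule t2 for both groups. But the link between control posttest and programme entry is a stated rule, not an omitted detail. Second, since only posttest completers reach follow-up and the raffle sits there, the posttest already leads indirectly to the raffle in both arms. It would be wrong to say that only controls have a reason to answer. Controls do have an additional one, access to iJobs, so detaching the questionnaire from enrolment altogether could lower their response.

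**Conclusion.** The point holds as a flaw in how control outcomes are collected. As written, they are observed conditional on taking up the delayed programme, and the planned model may not correct the resulting selection because its likely drivers arise after baseline and go unrecorded at t2. That these drivers explain the missing posttests is an inference from the procedure, not a reported fact.

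The scope for bias is real: about a quarter of pretested controls and nearly half of the pretested intervention arm lack a posttest in the interim data, under different selection rules that have no reason to cancel. The net bias has no determinable sign or size. The 0.13 SD and opposite 0.09 SD figures only illustrate an assumed 0.5 SD gap in raw completer means. The change is worth making because it is cheap and does not depend on knowing the direction.

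**What to change.** 1. At t2, email the posttest link to every randomised control by the route already used for their baseline. State that an answer is wanted whether or not they start iJobs or have found work.
2. Keep the in-module questionnaire as a second route for controls who enter, so that the existing incentive is not lost.
3. Ask the existing employment question at t2, so that finding work during the wait is on record.
4. Give a raffle entry for the t2 posttest in both arms.
5. Reconcile the t2 timing, so that the date of the email is defined. The Figure 2 legend and Table 1 footnote put it within a week of iJobs for both groups, while the text has controls reaching their questionnaire when their programme opens two weeks after the intervention group finishes.

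The cost is one extra email per control, one added question and a changed raffle condition. There may be slightly less incentive to complete the one-month follow-up. Two sessions have already been run, so the trial would contain two collection routes; recording route and session for each posttest would let this be examined.
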